# Efficacy of prophylactic methylprednisolone on reducing the risk of post-extubation stridor in patients after an emergency intubation: study protocol for a randomized controlled trial

**DOI:** 10.1186/s13063-020-04994-9

**Published:** 2021-01-06

**Keywords:** Post-extubation stridor, Corticosteroid, Emergency airway management, Multicenter, Randomized controlled trial

## Abstract

**Background:**

Post-extubation stridor (PES) is one of the most common complications of invasive respiratory support, with severe cases leading to possible extubation failure (reintubation within 48 h) and increased mortality. Previous studies confirmed that prophylactic corticosteroids play an important role in reducing the risk of PES and extubation failure. However, few studies have looked at the efficacy of corticosteroids on preventing PES in patients after an emergency intubation.

**Aim:**

To evaluate whether a single dose of methylprednisolone given over a set timeframe before extubation is effective in preventing PES in patients after an emergency intubation.

**Methods:**

A multicenter, randomized, placebo-controlled trial will be performed in an emergency department (ED) setting. The trial will include 132 patients who fail a cuff-leak test (CLT) prior to the intervention. Patients will be randomly assigned to either intravenous methylprednisolone (40 mg) or placebo 4 h prior to extubation. Other eligible patients who pass the CLT will be included in a non-intervention (observation) group. The primary endpoint is the incidence of PES within 48 h after extubation. Secondary endpoints include oxygen therapy, respiratory support requirements, reintubation secondary to PES, adverse effects within 48 h after extubation, hospital length of stay, and hospital mortality.

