### Intervention, control, and observation groups

Once eligible patients successfully pass a spontaneous breathing trial (SBT), a CLT will be performed to evaluate their risk for developing PES. Patients who had a cuff-leak volume (CLV) less than 24% of vital volume will be included in the intervention arm, where they will be randomly allocated to either the corticosteroid group or the placebo group. The planned extubation will be implemented within 6 h after allocation. Patients in the corticosteroid group and placebo group will be treated with an intravenous injection of methylprednisolone 40 mg (corticosteroid) or an equivalent volume of isotonic saline (placebo) 4 h prior to extubation. Patients with a CLV > 24% of tidal volume will serve as a control group, where extubation will be performed within 2 h after CLT completion.

All other standard precautions or treatments will be implemented in all patients.

Precautions include gentle extubation to avoid laryngotracheal mucosal injury, strict endotracheal tube (EET) fixation to avoid repeated friction between the EET and laryngotracheal mucosa, and EET nursing to reduce contamination risk. Any treatments for PES will be applied in accordance with each patient’s condition, including oxygen therapy with inhaled corticosteroid for mild airway edema and intravenous administration of hydrocortisone (100 mg) for moderate airway edema. Non-invasive ventilation or re-intubation will be carried out as clinically indicated if the above treatments are ineffective.

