### Study endpoints

The primary endpoint is the occurrence of PES within the first 48 h after extubation. Secondary endpoints include oxygen therapy after extubation, respiratory support requirements, reintubation secondary to PES within 48 h after extubation, and adverse effects (glycemic change, gastrointestinal bleeding or neuropsychiatric events). Clinical assessments will be done at 5, 15, 30, and 60 min, and then at 3, 6, 12, 24, 36, and 48 h after extubation. Hospital length of stay and hospital mortality will also serve as secondary endpoints (see Fig. 2 for study flow chart).

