## Discussion

Endotracheal intubation remains a challenging procedure, with multiple potential complications such as mucosal edema, ulcerations, or vocal cord injuries [6]. Although most complications are generally reversible, some patients develop severe symptoms [19]. Previous reviews showed the incidence of PES varied widely from 1.5 to 26.3%, and the incidence of reintubation due to laryngeal edema or PES was also quite variable at 1.1–10.5% [6]. While a recent study reported 29% of the patients intubated on an emergency basis had symptoms of stridor on extubation, 45% of these patients who required reintubation had symptoms of post-extubation upper airway obstruction [7], illustrating that PES and extubation failure were much more common in ED patients. Moreover, a study conducted among ED intubated patients showed 35% under multiple intubations, which was associated with a higher incidence of adverse events [20].

The type and dose of prophylactic corticosteroid used varied in adult populations. There were over 10 corticosteroid treatments reported in previous studies, all with different dosing and timings [5]. Although several studies found a multiple dose strategy may be more efficient than a single-dose strategy [1, 18, 21, 22], this is not optimal for ED use due to relative complexity over a single dose. In addition, a multiple dose strategy requires a longer pre-extubation period, which may cause unnecessary delays and increase the risk of complications in the ED setting. Methylprednisolone achieved a peak plasma concentration at about 0.8 h after intravenous administration [11] and possesses a half-life of approximately 2.5 h [23]. The pharmacology of methylprednisolone makes it a good choice for a single-dose, ED-based strategy.

Although few studies reported severe complications associated with prophylactic corticosteroids before extubation [10, 18, 21, 24, 25], a recent study led by Kuriyama [22] reported significantly increased blood glucose levels caused by corticosteroid use, especially among patients with underlying diabetes mellitus. Hyperglycemia, considered as an adaptive-stress response, is frequently present in critically ill patients [26]. A 2-day monitoring for the changes in blood glucose after methylprednisolone treatment will be implemented in our study, with temporary insulin therapy implemented if blood glucose levels increase more than 100 mg/dl.

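### The adverse-effect window starts at different points in different sections, and the abstract's version leaves out the roughly 4 h between injection and extubation

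*Protocol article*

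**What the plan says.** The protocol article touches the timing of adverse effects in four places.

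- **Abstract, Methods.** The secondary endpoints include "adverse effects within 48 h after extubation". This is the only place where a window is attached to adverse effects as a whole.
- **Study endpoints.** The components are named: "adverse effects (glycemic change, gastrointestinal bleeding or neuropsychiatric events". The 48 h limit in that sentence belongs to reintubation, and none is given for adverse effects. The next sentence reads "Clinical assessments will be done at 5, 15, 30, and 60 min, and then at 3, 6, 12, 24, 36, and 48 h after extubation".
- **Data collection and management.** Adverse effects are listed for each enrolled patient, with no start or end time, and the item is restricted to those caused by corticosteroids.
- **Discussion.** "A 2-day monitoring for the changes in blood glucose after methylprednisolone treatment will be implemented in our study". This clock starts at the drug, not at extubation.

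The section on intervention, control and observation groups gives methylprednisolone or "an equivalent volume of isotonic saline (placebo) 4 h prior to extubation", and adds: "The planned extubation will be implemented within 6 h after allocation". The Discussion puts the "peak plasma concentration at about 0.8 h after intravenous administration" and states that the drug "possesses a half-life of approximately 2.5 h".

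**The concern.** A safety comparison of a drug against placebo would normally begin when the drug is given. Here the one stated window for adverse effects opens about 4 h later, at an event that happens after randomisation and might not happen at all. Three things are at stake.

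1. Bleeding and neuropsychiatric events in the gap fall outside the abstract's endpoint, and the glucose clock in the Discussion does not rescue them.
2. A randomised patient who is injected but not extubated has no safety window, although Randomization and blinding promises intention-to-treat for all analyses.
3. With two clocks and two undated lists, sites could apply different rules, and the choice could be settled after data are seen.

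Separately, recording only effects attributed to corticosteroids asks staff who do not know the allocation to decide whether a corticosteroid caused the event.

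**Working it through.** The article gives no figure of its own on this point to reproduce. The check sets the clocks side by side and then applies the article's pharmacology to the gap.

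**Inputs.** Injection at time 0; extubation at 4 h (intervention section); abstract window of 48 h from extubation; glucose monitoring of 2 days from treatment (Discussion); plasma peak at about 0.8 h and half-life of about 2.5 h (Discussion).

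**The clocks, in hours after injection**

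| Source | Applies to | Start | End |
|---|---|---|---|
| Abstract, Methods | all adverse effects | 4 | 4 + 48 = 52 |
| Study endpoints, listed assessments | clinical assessments | just after 4 (5 min) | 52 |
| Discussion | glucose | 0 | 48 |
| Study endpoints, definition | adverse effects | not stated | not stated |
| Data collection and management | adverse effects | not stated | not stated |

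The abstract's window and the glucose clock overlap from 4 to 48 h (44 h) and differ by 4 h at each end.

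**What lies in the gap from 0 to 4 h**

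- Peak to opening of the abstract's window: 4 − 0.8 = 3.2 h.
- Level at extubation relative to peak: 2^(−3.2/2.5) = 0.41.
- Share of total plasma exposure elapsed by extubation, with simple exponential decay: 1 − 2^(−4/2.5) = 0.67.

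**Sensitivity**

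| Assumption | Level at 4 h relative to peak | Exposure elapsed by 4 h |
|---|---|---|
| Half-life 2 h (assumed) | 33% | 75% |
| Half-life 2.5 h (stated) | 41% | 67% |
| Half-life 3 h (assumed) | 48% | 60% |
| Half-life 2.5 h, first-order input fitted to a 0.8 h peak | 45% | 64% |

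Under each assumption the peak precedes the window, and between 60% and 75% of exposure has elapsed when it opens.

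**Effect of moving the start.** Counting from injection lengthens the window from 48 to 52 h. The added share is 4/52 = 7.7% of the longer window. The sample size calculation does not use the safety window, so it does not change.

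**The case against.** The strongest reply is that the article as a whole does not confine adverse effects to the period after extubation. The window appears in one clause of the abstract, the main text leaves adverse effects undated, and glucose, the harm that the Discussion singles out, is followed from treatment. **This stands.** A reader might infer that every adverse effect is counted only from extubation; that is true of the abstract, not of the article.

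Nor can it be said that nothing is recorded earlier. The schedule figure is not shown, and vital signs and oxygen saturation are collected throughout. **This also stands**, but the gap concerns which events count toward the endpoint, and the abstract fixes that explicitly.

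A third reply is that plasma exposure is not harm. **This is correct.** It is tempting to read the 67% as the share of harms missed, or to conclude that the safety comparison is biased toward no difference. The article gives no time course for any of the named effects, the window is the same length in both arms, and it still spans about 4 to 52 h after dosing. An event that began in the gap and was still present at 5 min could be seen then. Neither the size nor the direction of a bias is shown.

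Two further inferences go too far. The Discussion sentence names methylprednisolone, but with therapists blinded it cannot safely be read as monitoring one arm only. The abstract links adverse effects to risk stratification without making them central to the trial.

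Finally, patients have passed a breathing trial and extubation is planned soon after allocation, so injected but unextubated patients may be few. Their number cannot be known from the article, and a rule for them is still needed.

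**Conclusion.** The point holds as an inconsistency with a concrete consequence. The adverse-effect window runs from extubation in the abstract, from treatment for glucose in the Discussion, and is undefined in Study endpoints and in Data collection and management. Followed as the abstract states it, bleeding and neuropsychiatric events in the roughly 4 h after injection are not counted, and a patient who is never extubated has no window. Those hours hold the plasma peak and about two thirds of plasma exposure (60% to 75% for assumed half-lives of 2 to 3 h). This rests on the stated half-life, simple exponential decay and an injection-to-extubation interval of 4 h. The number of events lost cannot be derived from the document. The case for change is that the correction is cheap and removes an ambiguity, not that a bias has been demonstrated. The attribution wording is a lesser, related weakness.

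**What to change.** Reconcile the abstract, Study endpoints, Data collection and management, and the Discussion around a single definition:

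- The window starts at study-drug injection and ends 48 h after extubation, or 48 h after injection in a patient who is not extubated.
- It is identical in both randomised arms, and the glucose sentence in the Discussion refers to study drug rather than to methylprednisolone.
- The reference glucose is taken before injection, so that glycemic change is measured from an untreated value.
- Every event named in Study endpoints is counted regardless of presumed cause; the restriction to effects of corticosteroids is removed from the data-collection list.

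The cost is a wording change, a start time on the case report form, and slightly more events to record. Treatment, sample size and primary endpoint are unaffected. According to Trial status, recruitment was only due to begin around publication.

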**Discussion:**

Patients who are intubated on an emergency basis have a higher risk of intubation-related complications. Previous studies have examined treatment regimens involving more than 10 different variations on corticosteroid treatments for PES prevention, while for ED therapy, only a simple and effective treatment would be appropriate. Corticosteroid administration is usually accompanied by adverse effects; thus, this study will be important for further risk stratification among intubated ED patients.

**Trial registration:**

Chictr.org.cn ChiCTR2000030349. Registered on 29 February 2020.

**Supplementary Information:**

The online version contains supplementary material available at 10.1186/s13063-020-04994-9.

## Background

Endotracheal intubation with mechanical ventilation is a common life support method in emergency resuscitation. However, intubation/extubation and invasive mechanical ventilation may lead to the development of complications such as post-extubation stridor (PES) or extubation failure (defined as reintubation within 48 h). Both of these complications are associated with a higher risk of ventilator associated pneumonia, prolonged hospital length of stay and increased mortality [1].

Corticosteroids have a broad anti-inflammatory effect which is well described in previous studies [2, 3]. They also have a vasopressor effect that contributes to reduced airway edema and less microvascular fluid leakage [4], which may help prevent laryngeal edema and PES. While a large body of evidence has revealed that prophylactic corticosteroids effectively reduce the incidence of PES and reintubation among high-risk patients [5], few studies have evaluated their effectiveness in patients after an emergency intubation. Due to the large ED population and impatient ward shortage, many patients are both intubated and extubated while remaining in the ED setting. Comparing with the previous studies developed in intensive care units (ICUs) [6], Shinohara [7] found the incidence of PES was higher in patients intubated on an emergency basis. This may due to multiple factors, including lack of familiarity with a patient’s history, limited time for airway evaluation and management, contraindications to many sedative agents due to an unstable clinical condition (e.g., hypotension or altered mental status), massive intravenous fluid therapy, or patient-endotracheal tube size mismatch.

Ideally, patients at high risk for PES should be identified before extubation. The cuff-leak test (CLT), defined as the difference in the actual tidal volume before and after cuff deflation, has been proposed for this purpose [8, 9]. Previous studies described a cuff leak volume less than 110 ml or 24% of tidal volumes as insufficient [10–12], and evidence showed absent or insufficient cuff leak volume suggested an increased risk of PES and extubation failure [8]. Several studies showed the CLT has a good specificity but poor sensitivity, and the accuracy for predicting PES varied with different studies [13–15]. Moreover, the measured tidal volume could also be influenced by other factors such as system compliance or airflow resistance [13]. However, the CLT is still preferred as it has been showed to decrease the risk of PES and reintubation [9].

We conceived the present protocol in order to evaluate whether a single dose of methylprednisolone given over a set timeframe before extubation is effective in reducing the incidence of PES in patients who had been intubated on an emergency basis and were approaching extubation. We hope to answer this question through a multicenter, double-blind, randomized controlled trial.

## Methods

### Trial design and setting

This is an investigator-initiated, multicenter, superiority, randomized controlled trial that will include 132 participants in intervention arm. Six large tertiary hospitals in China will be involved in this trial. This study was prospectively registered with Chictr.org.cn on February 29, 2020 (identifier: ChiCTR 2000030349). The Ethics Committee of Peking Union Medical College Hospital, Chinese Academy of Medical Science, and Peking Union Medical College in Beijing has approved the trial protocol. The schedule of enrollment, intervention, data collection, and assessment follows the Standardized Protocol Items: Recommendations for Interventional Trials (SPIRIT) guidelines (see Fig. 1 for checklist and Additional File 1 for more details).

**Fig. 1 Fig1:**
[figure not shown]
Standard Protocol Items: Recommendations for Interventional Trials (SPIRIT) schedule of enrolment, intervention, and assessments. Anthropometric data: age, gender, body mass index (BMI). Asterisk indicates the following: ABGs, collected for necessity only. Baseline variables: GCS score, APACHE II score, vital signs. Primary endpoint: occurrence of PES. Secondary endpoints (a): post-extubation oxygen therapy, respiratory support requirement, reintubation secondary to PES, adverse effects. Secondary endpoints (b): hospital length of stay and hospital mortality. Continuous points: SaO_2_ and PETCO_2_

### Study population

Patients will be eligible for inclusion if they are aged 18–80 years, admitted into the emergency department (ED), and intubated emergently for one of the following conditions: (1) severe traumatic injury, (2) Glasgow Coma Scale (GCS) score < 8, (3) hypoventilation, (4) persistent hypoxemia (SaO_2_ ≤ 90%) despite supplemental oxygen, (5) persistent hypotension despite vasopressor treatment, or (6) cardiac arrest. Since most participants in our study will have no capacity to make decisions, written informed consent will be acquired from each patient’s next of kin prior to inclusion. Patients or their next of kin will be informed of the purpose, procedures, potential risks, and benefits of the study. Participants will be allowed to withdraw from the trial at any time without consequence.

Patients will be excluded if they meet at least one of the following criteria: pregnant or breastfeeding, chronically treated with corticosteroids or other anti-inflammatory drugs, extubated for patient comfort or on family request, unplanned or self-extubation, vocal cord dysfunction, deep sedation (defined as a Richmond Agitation-Sedation Scale (RASS) score ≤ − 4), or those diagnosed with gastrointestinal hemorrhage within the past 3 months.

There will be a research coordinator at each hospital to promote and monitor the trial.

### Intervention, control, and observation groups

Once eligible patients successfully pass a spontaneous breathing trial (SBT), a CLT will be performed to evaluate their risk for developing PES. Patients who had a cuff-leak volume (CLV) less than 24% of vital volume will be included in the intervention arm, where they will be randomly allocated to either the corticosteroid group or the placebo group. The planned extubation will be implemented within 6 h after allocation. Patients in the corticosteroid group and placebo group will be treated with an intravenous injection of methylprednisolone 40 mg (corticosteroid) or an equivalent volume of isotonic saline (placebo) 4 h prior to extubation. Patients with a CLV > 24% of tidal volume will serve as a control group, where extubation will be performed within 2 h after CLT completion.

All other standard precautions or treatments will be implemented in all patients.

Precautions include gentle extubation to avoid laryngotracheal mucosal injury, strict endotracheal tube (EET) fixation to avoid repeated friction between the EET and laryngotracheal mucosa, and EET nursing to reduce contamination risk. Any treatments for PES will be applied in accordance with each patient’s condition, including oxygen therapy with inhaled corticosteroid for mild airway edema and intravenous administration of hydrocortisone (100 mg) for moderate airway edema. Non-invasive ventilation or re-intubation will be carried out as clinically indicated if the above treatments are ineffective.

### Study endpoints

The primary endpoint is the occurrence of PES within the first 48 h after extubation. Secondary endpoints include oxygen therapy after extubation, respiratory support requirements, reintubation secondary to PES within 48 h after extubation, and adverse effects (glycemic change, gastrointestinal bleeding or neuropsychiatric events). Clinical assessments will be done at 5, 15, 30, and 60 min, and then at 3, 6, 12, 24, 36, and 48 h after extubation. Hospital length of stay and hospital mortality will also serve as secondary endpoints (see Fig. 2 for study flow chart).

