### Sample size calculation

We used a chi-squared statistical analysis of minimum sample size required to evaluate the effect of corticosteroids on our study outcomes. Cheng [10] showed that either a single or multiple doses of methylprednisolone 6 h before extubation reduced the incidence of PES compared to placebo (11.6%/7.1% vs 30.2%). Cheng [11] later reported that a single dose of methylprednisolone 4 h before extubation significantly reduced the incidence of PES from 39.4 to 15.8%. Other studies treating with prophylactic dexamethasone showed that it decreased the incidence of PES from 27.5–30.2 to 8.8–11.5% [12, 16]. We therefore anticipate an incidence of PES of 10% in the treatment group and 30% in the placebo group. With an 80% power to detect a difference and a two-sided alpha of 0.05, we anticipate needing 59 subjects in each group. Assuming a drop-out rate of 10%, we calculate a total minimum sample size of 132 subjects.

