### Data collection and management

For each participant, anthropometric data (gender, age, body mass index (BMI)) and baseline characteristics such as GCS score, Acute Physiology and Chronic Health II (APACHE II) score, vital signs (blood pressure, heart rate, respiratory rate, blood oxygen saturation and temperature), and arterial blood gases (ABGs) will be recorded as long as the patients are in-hospital. Arterial blood oxygen saturation (SaO_2_), as well as end tidal carbon dioxide (PETCO_2_) if available, will be continuously recorded. In order not to cause unnecessary pain to patients, ABGs will be collected when deemed clinically necessary during follow-up, while other baseline characteristics will be recorded at set times.

We will also record incidence of the following for each enrolled patient:
PES, defined as a presence of an audible high-pitched sound with respirationOxygen therapy after extubation (e.g., nasal catheter, reservoir mask or venturi mask)Requiring a respiratory support, as defined by:
Presence of respiratory acidosis (an arterial pH of less than 7.35 with a partial pressure of arterial carbon dioxide of more than 45 mmHg)Clinical signs of increased respiratory effort (use of accessory muscles, intercostal retractions, or paradoxical motion of the abdomen)Respiratory rate > 30 breaths/min for two consecutive hoursHypoxemia (SaO_2_ of < 90% with an FiO_2_ > 50%)Reintubation secondary to PESAdverse effects due to corticosteroidsHospital length of stayHospital mortality.

Clinical data will be collected locally via the Research Electronic Data Capture (REDCap) system, an Internet-based electronic case report form (CRF). The research coordinators at each hospital will form a steering committee, which provides training and reviews study processes, to improve adherence to the protocol and resolve problems. In addition, they will regularly audit CRFs and contact responsible medical staff members every 3 months to ensure data quality and accuracy. All data use will be limited to study analysis only, and no individuals’ personal information will be published. Data confidentiality will be under the supervision of the study coordinators and the Ethics Committee of Peking Union Medical College Hospital.

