### Statistical methods

The primary endpoint will be analyzed on an intention-to-treat basis, regardless of whether subjects complete their originally allocated treatment study protocol. Any reasons for protocol violations will be recorded and described. All *p* values will be two-tailed, and significance will be a *p* value < 0.05. Data will be presented as frequencies and percentages for categorical variables. Continuous variables will be expressed as means with standard deviations (when normally distributed) or as medians with interquartile ranges (for skewed distribution). Student’s *t* test (normal distribution) or Mann-Whitney *U* test (skewed distribution) will be used for group comparisons. Categorical variables will be compared using Pearson’s chi-squared test or Fisher’s exact test as appropriate. Statistical uncertainty will be expressed in terms of a relative risk and 95% confidence intervals.

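### If glycemic change is analysed as a continuous change, adjusting for starting glucose would be more precise than the unadjusted tests the protocol states; a minor gain on one secondary safety outcome

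*Protocol article*

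**What the plan says.** Three parts of the protocol article describe the glucose outcome.

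- **Study endpoints** names, among the secondary endpoints, "adverse effects (glycemic change, gastrointestinal bleeding or neuropsychiatric events". It gives no metric, time point or reference reading.
- **Discussion** promises that "A 2-day monitoring for the changes in blood glucose after methylprednisolone treatment will be implemented in our study". The trigger it gives for insulin is also expressed as a rise, of over 100 mg/dl.
- **Data collection and management** introduces its outcome list with "We will also record incidence of the following for each enrolled patient", and corticosteroid adverse effects are one item on that list.

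**Statistical methods** sets tests by type of variable. For continuous variables, Student's t test for normal data or the Mann-Whitney "test (skewed distribution) will be used for group comparisons". For the rest, "Categorical variables will be compared using Pearson’s chi-squared test or Fisher’s exact test as appropriate". No method that adjusts for a baseline value is named, and no sentence assigns a test to glucose specifically.

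**The concern.** A change needs a starting value, and so does a rise expressed in mg/dl. If that reading exists for each patient, the analysis can use it in two ways: subtract it and compare the differences, or adjust for it in a regression.

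Subtraction fixes the coefficient on the starting value at 1. When the two readings are only moderately correlated, that corrects too much. Patients who start high tend to fall and those who start low tend to rise, whichever treatment they receive, and this movement stays in the comparison as noise. The Discussion itself says that stress hyperglycemia is common in critically ill patients, so a moderate correlation is plausible, though the document does not measure it.

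What is at stake is precision. Glucose is the steroid harm that the Discussion treats at most length and the only one for which it describes specific monitoring. A wider interval makes a real rise harder to see. Randomization is stratified by sex only, so starting glucose can differ between arms by chance, and a change score lets part of that difference through.

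**Working it through.** **The plan's own figure.** The sample size concerns post-extubation stridor: "We therefore anticipate an incidence of PES of 10% in the treatment group and 30% in the placebo group". With 80% power and two-sided alpha 0.05, the unpooled formula gives (1.960 + 0.842)² × (0.3×0.7 + 0.1×0.9) / 0.2² = 7.849 × 0.30 / 0.04 = 58.9, so 59 per group. Allowing for 10% dropout, 59/0.9 = 65.6, so 66 per group and 132 in total. Both stated figures reproduce. No figure is stated for glucose; 59 per group is used below only as the analysed size.

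**Inputs for the comparison.** The document gives no glucose SD and no correlation between starting and follow-up glucose. Take a common SD (sigma) at both times and correlation rho, assumed between 0.3 and 0.9.

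**Variance per patient.**
- Change score: 2·sigma²·(1 − rho)
- Adjusted for starting glucose (ANCOVA): sigma²·(1 − rho²)
- Ratio, ANCOVA to change: (1 − rho²) / [2(1 − rho)] = (1 + rho)/2

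**Power.** Take the effect for which ANCOVA has 80% power at 59 per group. The change-score test then has power of about Φ(2.802·√[(1+rho)/2] − 1.960).

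| rho (assumed) | Change variance / sigma² | ANCOVA variance / sigma² | Ratio | Standard error, change relative to ANCOVA | Power of change-score test |
|---|---|---|---|---|---|
| 0.3 | 1.40 | 0.91 | 0.65 | 1.24 | 61.7% |
| 0.5 | 1.00 | 0.75 | 0.75 | 1.155 | 67.9% |
| 0.7 | 0.60 | 0.51 | 0.85 | 1.085 | 73.3% |
| 0.9 | 0.20 | 0.19 | 0.95 | 1.026 | 78.0% |

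**Dependence on equal variances.** With starting SD s0 and follow-up SD s1, the change variance minus the ANCOVA variance is (s0² + s1² − 2·rho·s0·s1) − s1²(1 − rho²) = (s0 − rho·s1)², which is never negative. The direction therefore holds in large samples without equal variances; the sizes in the table do not.

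**Chance imbalance.** With 66 per arm, the standard error of the difference in mean starting glucose is √(2/66) = 0.17 SD. An imbalance of at least 0.2 SD in either direction then has probability of about 25% (z = 0.2/0.174 = 1.15). It moves the change-score estimate by 0.2(1 − rho) SD: 0.14 at rho 0.3, 0.10 at 0.5, 0.06 at 0.7 and 0.02 at 0.9.

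**The case against.** The strongest reply is that the protocol never says a t test or Mann-Whitney test will be run on the glucose change. The tests are a general menu. Glycemic change stands beside two event-type harms, and adverse effects are on a list recorded as incidence. An incidence would go to the chi-squared or Fisher test, where these variance figures do not apply. This stands in part: the test on the change is an inference. It does not settle the matter, because the same list contains hospital length of stay, which is not an incidence, and both Study endpoints and the Discussion speak of change.

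Second, covariate adjustment of a secondary safety variable is commonly left to an analysis plan, which is not shown. That is why the point is a suggestion and not an omission. Its basis is what the article does state: unadjusted tests for continuous variables.

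Third, the sizes rest on an assumed correlation, equal variances, one follow-up value and a mean-scale analysis. They do not cover the Mann-Whitney test or a peak over two days, and insulin given after large rises would alter later readings. All of this stands.

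A reader might infer more than the document supports:
- **That the change-score comparison is biased or invalid.** Under randomization it is unbiased with valid type I error. For rho above 0.5 it is also more precise than comparing unadjusted follow-up values, since 2(1 − rho) is then below 1.
- **That glucose is the main harm measure.** The three adverse effects are not ranked.
- **That a starting imbalance passes into the estimate in full.** Only the fraction (1 − rho) does.

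**Conclusion.** The point holds as a conditional one. If glycemic change is analysed as a continuous change score with the stated two-sample tests, the comparison is valid but less precise than one adjusted for starting glucose. Under equal variances, adjustment removes about 35% of the variance at rho 0.3, 25% at 0.5, 15% at 0.7 and 5% at 0.9. At the upper end the gain is negligible.

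This is a small improvement to one secondary safety outcome for which the trial was not powered. A reader should not take it as a fault in the trial's main result: the analysis of post-extubation stridor, the 59 per group and the total of 132 are untouched.

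**What to change.** Add one sentence to Statistical methods: glucose at a pre-stated follow-up time will be analysed by linear regression on arm and pre-injection glucose, log-transformed if skewed, and reported as an adjusted difference with its 95% confidence interval. On the same scale, using the change as the outcome in that regression gives the identical arm estimate, so the endpoint's name can stay. Report any incidence of a large rise as a separate descriptive count, which also clears up whether the outcome is a change or an incidence.

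The cost is small. The pre-injection reading, which the change already requires, must be recorded on the case report form in both arms; the baseline variables named in Data collection and management do not include glucose. Beyond that there is only minor analysis work. No extra patients are needed, and the sentence should be fixed before unblinding.
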